### Exclusion criteria

Patients will be excluded if they meet any of the following exclusion criteria:History of bariatric surgery or extensive gastrointestinal surgical procedures.History of excessive alcohol consumption, defined as ethanol amounts converted from alcohol intake by men and women > 40 g/d and 20 g/d, respectively, for more than 5 years, or alcohol consumption > 80 g/d within 2 weeks (alcohol intake [g/d] = alcohol consumption [mL/d] × alcohol content [%] × 0.8).History of taking amiodarone, methotrexate, tamoxifen, and glucocorticoids, or chronic use of any other drug that may induce liver injury.Diagnosed with specific diseases that cause adiposis hepatica, including infections by hepatitis C virus genotype 3, hepatolenticular degeneration, autoimmune hepatitis, total parenteral nutrition, abetalipoproteinemia, congenital lipodystrophy, and chylous diarrhoea.Diagnosed with confirmed or suspected malignant tumours or severe cardiorespiratory, cerebral, or metabolic diseases.Pregnancy.Not willing or unable to provide consent for participation in the study.

### Outcome measures

The primary outcome of this study is the complete remission rate of NAFLD one year postoperatively, as defined by liver fat fraction (LFF) < 5% on abdominal MRI.

Secondary outcomes are as follows:(i)changes in NASH and liver fibrosis biopsy findings, including the NAS (NAFLD activity score) [16] and SAF scores (steatosis [S], activity [A], and fibrosis [F])[17] one year postoperatively.(ii)changes in body weight and abdominal adipose weight, indicated by changes in the following parameters at each follow-up:percent excess weight loss (%EWL): %EWL = ([initial weight] – [postoperative weight])/([initial weight] – [ideal weight]) (ideal weight is defined as a body mass index [BMI] of 25 kg/m^2^ at each follow-up point)percentage of total weight loss (%TWL): %TWL = ([initial weight] – [postoperative weight])/([initial weight]) × 100(III)resolution of obesity-related comorbidities: blood glucose levels, lipid levels, and liver enzyme levels.(iv)incidence of adverse health events.

### Data collection

A standard case report form was designed before the study and transferred to an electronic data capture (EDC) system (https://www.base-nafld.com). The EDC system provides a graphical user interface for data entry and has a validation component for data cross-checking and a reporting tool for descriptive analysis. Well-trained clinical research coordinators from Chuankang (Medicine Technology Co, Beijing, China) and Suzhou Plenitude (Bio-Medical Technology Co., Ltd., Jiangsu, China) will retrieve all required information from the medical records of included patients and upload them into the EDC system. Clinical research associates from Beijing Funhau Medicine Technology Co. are in charge of monitoring and providing feedback on the EDC system and for data quality control.

The case report form was designed to collect the following baseline and follow-up data (Table 1):Demographic data: study code, initial name, sex, date of birth, admission date, height, body weight, transumbilical abdominal circumference, smoking habits, and drinking habits.Disease history and medication usage: type 2 diabetes mellitus, hypertension, polycystic ovarian syndrome, and obstructive sleep apnoea hypopnoea syndrome; use of oral hypoglycaemic, insulin, anti-hypertensive medication, and lipid-lowering drugs.Preoperative examinations: routine blood tests and biochemical examinations, especially for ALT, AST, HbA1c, fasting blood glucose, fasting insulin levels, prothrombin activity time, and AFP; findings from abdominal ultrasonography and gastroscopy; and assessment of LFF levels from MRI.Surgical information: operation date, type of surgery, operation time, and surgical procedure information, including gastric pouch volume, Roux limb length, biliopancreatic limb length, stapler usage, and suturing.Liver pathology: findings from histopathological examinations of liver biopsy specimens obtained intraoperatively and one year postoperatively.Adverse events or serious adverse events.

**Table 1 Tab1:** Checklist of baseline and follow-up visits of patients enrolled in the Base-NAFLD study

	Visit 1 (Baseline)	Visit 2 (3-month intervals)	Visit 3 (6-month intervals)	Visit 4 (1-year intervals)	Visit 5 (2-year intervals)
Demographic data	●	●	●	●	●
Disease history and medication usage	●	●	●	●	●
Surgical information	●	✗	✗	✗	✗
Weight loss	✗	●	●	●	●
Routine blood tests	●	●	●	●	●
HbA1c	●	●	●	●	●
OGTT	●	✗	✗	○	✗
FBG	✗	●	○ ●	✗	●
Fasting insulin and fasting C-peptide	✗	○	○	●	○
Biochemical examination	●	●	●	●	●
Thyroid function	●	○	○	●	●
Serum iron and TIBC	●	●	○	●	●
Ferritin and folate and Vitamin B12	●	●	○	●	●
AFP	●	✗	✗	✗	●
Coagulation function	●	○	✗	●	●
Gastroscopy	●	✗	✗	○	○
C13 breath tests	●	✗	✗	○	○
Abdominal ultrasonography	●	●	○	○	○
Lower extremity vascular ultrasound	●	✗	✗	○	○
Abdominal MRI	●	●	●	●	●
Liver biopsy	●	✗	✗	●	✗
Adverse events	✗	●	●	●	●

Base-NAFLD, Bariatric Surgery for Non-alcoholic Fatty Liver Diseases in Individuals with Obesity; HbA1c, glycosylated haemoglobin; OGTT, oral glucose tolerance test; FBG, fasting blood glucose; TIBC, total iron-binding capacity; AFP, alpha-fetoprotein

●: Mandatory; ○: Optional; ✗: Not required

### Patient follow-up

According to the guidelines for the follow-up of patients undergoing bariatric surgery [18], follow-up visits at 3 months, 6 months, 1 year, and 2 years after surgery will be recommended to all patients. In each participating centre, follow-ups will be conducted by a research nurse or research doctor belonging to a multi-disciplinary team. Pertinent information will be obtained by either in-hospital visits, over telephone, or using WeChat—the most popular instant messaging app in China with over 1 billion users. Follow-up interviews have been designed to acquire information corresponding to the case report form (Table 1). Treatment-related adverse events and complications will be confirmed by all the researchers by a comprehensive review of involved medical records and details of follow-ups.

### Sample size determination

The Power Analysis and Sample Size software program (PASS, version 11.0 by NCSS, LLC) was used for sample size calculation, which was based on the estimated complete remission rate reported by previous retrospective studies [9–12] and the preliminary clinical results obtained from our centre. According to our preliminary data, 58 of the 69 patients (84%) who underwent bariatric surgery had preoperative underlying NAFLD, and the rate of complete remission was 55.2% three months postoperatively. To achieve a confidence interval width of 0.16 and an α value of 0.05 with a 78% complete remission rate, the estimated minimum sample size required for our study was 114. The withdrawal rate will be assumed to be 20% during follow-up; therefore, the sample size needed for this study will be at least 142 patients. Nevertheless, as this is an observational study, additional patients will be recruited for a subgroup analysis. According to the national registry in our country, the number of patients undergoing each type of surgery was found to be 82, 30, and 30 patients for the SG, RYGB, and OAGB groups, respectively.

### Statistical analysis

SPSS 20.0 (SPSS, Inc., Chicago, IL, USA) and R software (R version 3.6.3; R Foundation for Statistical Computing, Vienna, Austria) will be used to perform statistical analyses. Continuous data will be presented as mean (standard deviation) or median (minimum, maximum) values, and categorical data will be presented as numbers (proportions/frequencies/percentages). P-values < 0.05 will be considered statistically significant.Comparison between preoperative and postoperative parameters: For paired continuous data, the paired t-test (normally distributed variables) or Wilcoxon’s signed-rank (skewed variables) will be used for analysis, whereas for paired categorical data, the chi-square test or Fisher’s exact test will be used for analysis.Primary outcomes: The complete remission rate of NAFLD in obese patients, along with the corresponding 95% confidence interval will be reported.Sensitivity analysis: A sensitivity analysis will be conducted to investigate the differences between the three types of surgery and BMI subgroups in terms of complete remission rate of NAFLD. Continuous variables will be tested by a paired t-test or Wilcoxon’s signed-rank test for paired samples, and the association between covariates and main outcomes will be tested using the chi-square test or Fisher’s exact test.Development and validation of the prediction model: Before building the model, the dataset will be divided into a training set—three-quarters of the enrolled patients will be randomly assigned to this set—and a validation set—the remainder of the patients will be assigned to this set. A multivariable logistic regression model will be used in which the response variable will be complete remission of NAFLD. The model will be built using stepwise selection based on the Akaike information criterion. The training model will be subsequently applied to the validation set. The model performance of both the training and validation sets will be evaluated using C statistics for discrimination, and the goodness-of-fit will be evaluated using Hosmer–Lemeshow test. A calibration curve will also be developed to examine the model fit. For both the training and validation sets, the predicted risk will be plotted against the observed risk for each of the 10 risk percentiles created from the dataset. Calibration will be evaluated using the Hosmer–Lemeshow goodness-of-fit test and chi-square test based on the predicted risk deciles. Results will be displayed as a nomogram to provide clinicians with an intuitive and quantitative tool to predict the probability of complete NAFLD remission in obese patients.

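### Paired before/after categorical data are assigned the chi-square or Fisher's exact test, both of which ignore the pairing; a McNemar-type test is needed

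*Protocol article*

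**What the plan says.** The Statistical analysis section of the protocol article has an item on comparing parameters before and after surgery. For continuous measurements it names tests that respect the pairing: "For paired continuous data, the paired t-test (normally distributed variables) or Wilcoxon’s signed-rank (skewed variables) will be used for analysis". The same sentence then says that "for paired categorical data, the chi-square test or Fisher’s exact test will be used for analysis".

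The same two tests return in the sensitivity-analysis item for an ordinary unpaired purpose: "the association between covariates and main outcomes will be tested using the chi-square test or Fisher’s exact test". The threshold throughout is "P-values < 0.05 will be considered statistically significant". No test for paired categorical data is named anywhere in the document.

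The primary analysis does not use these tests: "The complete remission rate of NAFLD in obese patients, along with the corresponding 95% confidence interval will be reported".

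**The concern.** The plan recognises that the categorical data are paired and then names two tests for independent samples. This is a stated rule, not a detail left to an analysis plan, and an analysis plan that follows the protocol would inherit it.

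The tests could be run in two ways, and neither answers whether the proportion of patients with a condition changed after surgery.

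- **Before and after counts as two groups.** Each patient enters twice, as if 114 patients were 228 unrelated people. Status in the same patient is usually positively correlated over time, which makes the assumed variance of the difference too large and the p-value too large.
- **The before-by-after cross-table.** The test asks whether status before predicts status after. It can be highly significant when nothing has changed.

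The study is a before/after cohort without a non-surgical control, so within-patient change carries much of its secondary evidence. Table 1 requires disease history and medication use at every visit, and a liver biopsy at baseline and one year. The Discussion treats the biopsy changes as important secondary results. Comorbidity present or absent, medication use, NASH present or absent and fibrosis category would all fall under this rule if analysed as categories.

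**Working it through.** **Inputs.** The number of pairs is 114, the evaluable number in Sample size determination ("the estimated minimum sample size required for our study was 114"). The level is 0.05, taken as two-sided because the document does not say. All cell counts, prevalences and correlations below are assumptions, because the document gives none.

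**The plan's own figure.** The document gives no figure for the paired categorical tests. The 114 itself reproduces: the stated basis is "To achieve a confidence interval width of 0.16 and an α value of 0.05 with a 78% complete remission rate", and the exact (Clopper-Pearson) 95% interval at 78% first has a width of at most 0.16 at n = 114. With 20% withdrawal, 114/0.8 = 142.5, against the stated 142.

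**Notation.** a = condition present both times; b = resolved; c = new; d = absent both times; n = a + b + c + d.

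**Example 1, a real fall analysed as two groups.** a = 34, b = 12, c = 2, d = 66. Prevalence goes from 46/114 to 36/114.

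- Unpaired chi-square: (46 − 36)² / [2n·p̄(1 − p̄)], with p̄ = 82/228 = 0.360. This is 100/52.5 = 1.90, p = 0.17. Fisher's exact p = 0.21.
- McNemar: (b − c)²/(b + c) = 100/14 = 7.14. The numerator is the same, but the variance comes from the 14 patients who changed: 14 instead of 52.5.
- Exact McNemar: 2 × (1 + 14 + 91)/2¹⁴ = 212/16384, p = 0.013.
- Paired change: 10/114 = 8.8 percentage points, SE = √(14 − 100/114)/114 = 0.0318, 95% CI 2.5 to 15.0 points.

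**Example 2, no net change, analysed on the cross-table.** a = 36, b = 10, c = 10, d = 58. Prevalence is 46/114 both times.

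- Chi-square: n(ad − bc)² / [(a+b)(c+d)(a+c)(b+d)] = 114 × (2088 − 100)² / (46 × 68 × 46 × 68) = 46.0, p about 1e-11. Fisher's exact p is about 7e-12.
- McNemar: (10 − 10)²/20 = 0, p = 1.0.

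**Simulation over a range of within-patient correlations** (114 pairs; 20,000 runs, with exact McNemar on 4,000 of them). Entries are rejection rates at nominal 0.05.

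| Scenario | Correlation | Chi-square, two groups | McNemar | Exact McNemar | Chi-square, cross-table |
|---|---|---|---|---|---|
| No change, 40% both times | 0 | 0.048 | 0.047 | 0.031 | 0.049 |
| | 0.3 | 0.018 | 0.047 | 0.036 | 0.90 |
| | 0.5 | 0.006 | 0.055 | 0.029 | 1.00 |
| | 0.7 | 0.001 | 0.048 | 0.031 | 1.00 |
| Fall from 40% to 27% | 0 | 0.55 | 0.54 | 0.50 | 0.05 |
| | 0.3 | 0.56 | 0.70 | 0.64 | 0.89 |
| | 0.5 | 0.57 | 0.85 | 0.78 | 1.00 |
| | 0.7 | 0.58 | 0.99 | 0.97 | 1.00 |

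The two-group chi-square becomes more conservative as correlation rises and gains almost no power from the pairing. The cross-table chi-square responds to correlation whether or not the proportion changes.

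**The case against.** The strongest objections concern reach and size.

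- **Scope.** The primary outcome is one proportion with an interval, and the sample size is a precision calculation. Neither uses this rule. This stands.
- **Few named endpoints are clearly categorical.** Outcome measures describes comorbidity resolution through laboratory values ("resolution of obesity-related comorbidities: blood glucose levels, lipid levels, and liver enzyme levels"), which are continuous and already have paired tests. Percent weight loss is itself a change measure, adverse events have no preoperative counterpart, and NAS and SAF scores could go to the signed-rank test. This stands in part. The list of affected items is inferred from what is collected and from the stated aims of resolution and change in NASH. However, the plan itself provides a rule for paired categorical data and evidently expects to use it.
- **The two harms come from different layouts.** The article does not say which would be used, so they cannot both occur in one analysis. True, but both layouts are faulty.
- **The illustration sits near the threshold.** With a fall from 46 to 20 (28 resolved, 2 new), the two-group chi-square gives p of about 0.00015 and exact McNemar about 9e-7, so the conclusion is the same. This stands: the conclusion does not always reverse. It does not make the p-value right.
- **Chi-square may be shorthand for McNemar's chi-square.** This is weak. Fisher's test is not McNemar's small-sample partner, which is the exact binomial test on discordant pairs. The identical pair of tests is named for unpaired associations, and paired versions are named explicitly for continuous data.

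**Conclusion.** The rule is wrong as written. Whenever status before and after surgery is correlated within patients, either way of running the named tests gives an invalid p-value for change. Compared as two groups at an assumed 40% prevalence, the actual type I error falls to between 0.018 and 0.001 for correlations of 0.3 to 0.7. Power for a fall to 27% stays at 0.56 to 0.58, while exact McNemar has 0.64 to 0.97. On the cross-table, 90% to 100% of analyses with no change are declared significant over the same correlations.

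The size depends on prevalences and correlations that the document does not give. At zero correlation the two-group test is about right, though that is unlikely for the same patient's disease status. The consequence is confined to secondary before/after comparisons analysed as categories.

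**What to change.** Replace the clause on paired categorical data with wording such as: binary items will be compared before and after surgery with the exact McNemar test; unordered items with more than two categories with the Stuart-Maxwell or Bowker test; ordinal items such as NAS and SAF components with the Wilcoxon signed-rank test; and for each binary item the paired change in proportion will be reported with a 95% confidence interval. Keep the chi-square and Fisher's exact tests for the unpaired associations, where they belong.

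The exact McNemar test is somewhat conservative (actual level about 0.03 in the simulation), which is a further reason to report the interval alongside it.

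The cost is one sentence, settled before analysis. Both named packages run these tests, and no data, visits or patients are added.

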“Bariatric surgery for non-alcoholic Fatty Liver Diseases in Individuals with Obesity (Base-NAFLD)” is a prospective multicentre observational follow-up study. This study aims to adequately assess the effect of bariatric surgery on NAFLD remission in obese patients: (i) to demonstrate the effectiveness of bariatric surgery for NAFLD, including NASH, (ii) to explore the differences in the effectiveness among three types of surgery—sleeve gastrostomy (SG), Roux-en-Y gastric bypass (RYGB), and one anastomosis gastric bypass (OAGB), and (iii) to develop a predictive model for surgical treatment using internal and external validation cohorts. This study will provide a necessary and preliminary foundation for the early identification and targeted treatment of patients with NAFLD, who need to be referred for bariatric surgery for the management of obesity and metabolic diseases.

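### Surgery types and BMI subgroups are compared only on the yes/no remission cut, with no between-group analysis of the liver fat fraction that MRI already measures

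*Protocol article*

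**What the plan says.** - **Aim.** The second study aim in the Background is "to explore the differences in the effectiveness among three types of surgery": SG, RYGB and OAGB. The Discussion promises preliminary results on the choice of procedure.
- **Primary outcome.** Complete remission at one year, "as defined by liver fat fraction (LFF) < 5% on abdominal MRI" (Outcome measures). Neither the level of LFF nor its change appears among the secondary outcomes.
- **Comparison.** Under the label of a sensitivity analysis, the Statistical analysis section will "investigate the differences between the three types of surgery and BMI subgroups in terms of complete remission rate of NAFLD". The association tests named are chi-square and Fisher's exact. The tests named there for continuous variables are paired, so they compare a patient with himself or herself and not one procedure with another.
- **Prediction model.** The multivariable logistic model also takes complete remission as its response.
- **Data.** LFF levels from MRI are collected (Data collection), and Table 1 marks abdominal MRI as mandatory at all five visits.
- **Group sizes and level.** "82, 30, and 30 patients for the SG, RYGB, and OAGB groups, respectively" (Sample size determination), with "P-values < 0.05 will be considered statistically significant".

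**The concern.** The study uses a quantitative measure of liver fat and, for the comparison with its smallest groups, reduces it to one cut. A patient who falls from 40% to 6% then counts the same as one who does not change, while 4.9% and 5.1% count as different. The cut suits a descriptive remission rate. As the only scale for comparing procedures it may hide real differences in liver fat, and a non-significant result could be read as equal effectiveness in a field where, by the article's own account, there is no consensus on procedure.

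Patients are also not randomised to procedure. A comparison that ignores baseline LFF and BMI cannot separate the effect of the procedure from differences between the patients who receive it.

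**Working it through.** **1. The plan's own figure.** The inputs are "To achieve a confidence interval width of 0.16 and an α value of 0.05 with a 78% complete remission rate". The Clopper-Pearson width at 78% is 0.1601 for n = 113 and 0.1594 for n = 114, so "the estimated minimum sample size required for our study was 114" reproduces. Then 114/0.8 = 142.5, stated as 142. This calculation concerns the precision of the overall rate and says nothing about comparing procedures.

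**2. Evaluable groups.** "The withdrawal rate will be assumed to be 20% during follow-up". 82 × 0.8 = 65.6, about 66, and 30 × 0.8 = 24. The sum 66 + 24 + 24 is 114.

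**3. Model A, an assumption: each procedure shifts the whole LFF distribution.** One-year LFF is normal on some monotone scale with equal SD. SG remits at 0.78 and the comparator rate is assumed. Alpha is 0.05, taken as two-sided.

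- Binary power = Φ((|p1 − p2| − 1.96·s0)/s1), where s0 is the pooled and s1 the unpooled standard error.
- Continuous power = Φ(d/√(1/66 + 1/24) − 1.96), where d = |z(p1) − z(p2)| and √(1/66 + 1/24) = 0.2384.

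Example, 0.78 against 0.63:
- Binary: s0 = 0.1046 and s1 = 0.1110, so (0.15 − 0.2050)/0.1110 = −0.50, power 31%.
- Continuous: d = 0.772 − 0.332 = 0.440, and 0.440/0.2384 − 1.96 = −0.11, power 46%.

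SG against one bypass group, 66 v 24. Gains are in points, from unrounded power. The last two columns are simulated (4,000 runs); the floor ties the lowest 40% of the reference group's LFF values.

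| Comparator rate | d | Binary | Continuous | Gain | Gain, rank test | Gain, rank test with floor |
|---|---|---|---|---|---|---|
| 0.68 | 0.304 | 17% | 25% | 7 | 7 | 5 |
| 0.63 | 0.440 | 31% | 46% | 15 | 13 | 12 |
| 0.58 | 0.570 | 47% | 67% | 20 | 17 | 15 |
| 0.88 | 0.403 | 16% | 39% | 24 | 22 | 16 |
| 0.90 | 0.509 | 22% | 57% | 35 | 32 | 23 |
| 0.93 | 0.704 | 34% | 84% | 50 | 46 | 36 |

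With all three groups and both bypass groups shifted, the calculated gains for the same six rates are 10, 20, 24, 23, 35 and 44 points.

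Under this model the cut keeps φ(z)²/(p(1 − p)) of the information. At 0.78 that is 0.2961²/(0.78 × 0.22) = 0.51; at 0.90 it is 0.34.

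**4. Model B, also an assumption: procedures differ only in the share who remit.** Remitters' LFF is uniform from 1% to 5%; non-remitters' is 5% plus an exponential with mean 5. Three groups of 66/24/24, by simulation, with Model A beside it (KW = Kruskal-Wallis):

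| SG/RYGB/OAGB remission | A: chi-square | A: KW | B: chi-square | B: KW | B: ANOVA on log LFF |
|---|---|---|---|---|---|
| 72/86/86% | 31% | 61% | 29% | 17% | 18% |
| 70/89/89% | 57% | 90% | 56% | 30% | 34% |
| 84/70/70% | 37% | 56% | 38% | 20% | 23% |
| 87/66/66% | 69% | 91% | 69% | 39% | 46% |
| 78/65/91% | 48% | 82% | 49% | 26% | 27% |

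Under B the rank test is weaker than chi-square by 12 to 30 points. The same remission rates therefore give opposite answers, depending on how LFF behaves on either side of the cut.

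**5. BMI subgroups.** Their sizes are not given, so nothing can be computed.

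**The case against.** The strongest objection is Model B: the sign of the power difference is not fixed by the documents. This stands. A reader might infer that the plan throws away a definite 13 to 35 points of power. That range needs assumed comparator rates and a constant shift with equal SD, none of which the article supplies.

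Other points that stand:

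- **No power is promised.** The aim is to explore, the results are called preliminary, and the sample size was set by interval width alone. This is a question of efficiency, not a contradiction. The article also foresees extra patients for subgroup analysis. Under Model A with 82/30/30 evaluable, the simulated t-test gain for SG against one bypass group is still 9 to 43 points.
- **Remission is a legitimate scale.** It is the declared primary outcome and is easy to read clinically. Mean LFF is a different estimand. Nothing supports demoting remission, and the histological scores already grade steatosis at one year.
- **Not every patient need have a quantitative LFF.** Steatosis may be diagnosed by ultrasonography or pathology, and follow-up may be by telephone or WeChat, so a mandatory MRI can be missing in practice. A missing one-year MRI harms both analyses.
- **The cut is not at its worst at 78%.** Under Model A it keeps about 51% of the information there and less at higher rates.
- **The Discussion's statement on PDFF concerns the presence of steatosis.** The better support is its neighbouring statement that MRI is an accepted reference for hepatic fat content.

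The objection that LFF analyses are left to an unseen analysis plan carries less weight. The article does not stay silent: it names the endpoint and the tests for this comparison.

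**Conclusion.** The point holds as a limited one. The only stated comparison of procedures and BMI subgroups is on the dichotomised rate, unadjusted, although quantitative LFF is scheduled at baseline and one year.

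If procedures shift the whole LFF distribution, the cost is roughly 5 to 35 points of power for moderate differences in groups of about 66/24/24, and up to about 50 for extreme ones. If they differ only in the share who remit, the binary comparison can be the stronger. The documents do not say which holds. The case for change therefore does not rest on a power figure. The data are already scheduled, the two scales answer different questions, and a non-randomised comparison should take account of baseline LFF. The primary outcome and its confidence interval are not affected.

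**What to change.** - Keep LFF below 5% at one year as the primary outcome, and keep the remission comparison between procedures.
- In Outcome measures, name one-year LFF as a secondary outcome.
- In Statistical analysis, add a between-procedure analysis of continuous one-year LFF adjusted for baseline LFF and BMI. ANCOVA on log LFF would serve, or proportional-odds regression if values cluster near zero. Report estimates with 95% confidence intervals beside the remission differences.

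Cost: some wording and one more model, with no new patients, visits or scans. The downside is one more secondary result, on a scale less directly clinical than remission, and no guaranteed gain in power.

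### For continuous variables, the item comparing surgery types and BMI subgroups names only paired tests, which cannot compare independent groups

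*Protocol article*

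**What the plan says.** Three parts of the Protocol article's Statistical analysis section bear on this.

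- **Before/after item.** Paired methods are assigned here first: "For paired continuous data, the paired t-test (normally distributed variables) or Wilcoxon’s signed-rank (skewed variables) will be used for analysis".
- **Sensitivity-analysis item, purpose.** The item is meant "to investigate the differences between the three types of surgery and BMI subgroups in terms of complete remission rate of NAFLD".
- **Sensitivity-analysis item, methods.** One sentence gives two methods. The first half reads "Continuous variables will be tested by a paired t-test or Wilcoxon’s signed-rank test for paired samples". The second half reads "the association between covariates and main outcomes will be tested using the chi-square test or Fisher’s exact test".

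Elsewhere, Outcome measures defines the primary outcome as the "complete remission rate of NAFLD one year postoperatively, as defined by liver fat fraction (LFF) < 5% on abdominal MRI", which is a yes/no result for each patient. Sample size determination expects "82, 30, and 30 patients for the SG, RYGB, and OAGB groups, respectively". Patient recruitment makes clear that each patient has one of the three procedures. Aim (ii), in the Background, is to explore how effectiveness differs among them.

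**The concern.** The item's purpose is a comparison between different patients, but the only tests it gives for continuous variables are for paired data. A paired test needs two linked measurements on each unit. A sleeve patient has no partner in either bypass group, and a patient in one BMI subgroup has none in another. Both named tests also handle two sets of values, whereas surgery type has three groups.

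At stake is the continuous side of aim (ii). Weight loss (%TWL and %EWL), liver fat fraction on its own scale, and liver enzymes are continuous outcomes on which procedures could differ. The Discussion promises preliminary results on the choice of procedure. If the text is followed literally, these outcomes either get no between-procedure test or get separate within-procedure tests that do not address the question.

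**Working it through.** The main check is a reading of the text. Two short calculations mark out what is not affected.

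**1. Are the groups independent?** Yes. Each patient has one procedure, so the three surgery groups share no patients. BMI subgroups are likewise disjoint. Nothing in the article describes matching.

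**2. What each named method can do:**

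| Item | Question | Test named | Does it fit? |
|---|---|---|---|
| Before/after comparison | Change within patients, continuous | Paired t or signed-rank | Yes |
| Sensitivity analysis | Remission rate across surgery or BMI groups | Chi-square or Fisher's exact, if group counts as a covariate | Yes |
| Sensitivity analysis | Continuous variables across surgery or BMI groups | Paired t or signed-rank | No |

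**3. Is the right test named elsewhere?** No. The two-sample t-test, Mann-Whitney, ANOVA, Kruskal-Wallis and ANCOVA do not appear in the article.

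**4. Does the within-subgroup reading repair it?** The words about paired samples could mean before/after tests inside each subgroup. Let the mean change in group g be d_g. The paired test in group g addresses d_g = 0. The item's question is whether d_SG = d_RYGB = d_OAGB. Three separate tests of the first kind do not test the second. The percentage weight-loss measures show this plainly: each patient has one value per visit, already expressed relative to starting weight, so comparing procedures on them needs a test for independent samples.

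**5. Does the remission-rate test work in these groups?** Inputs from Sample size determination are 82, 30 and 30 patients, 20% withdrawal and a 78% remission rate. Evaluable numbers are 82 × 0.8 = 65.6, about 66, and 30 × 0.8 = 24 in each bypass group (66 + 24 + 24 = 114). In a simulation of 20,000 trials with a common true rate of 0.78, the three-group chi-square test at the 5% level rejected in 0.049 of them. It holds its level despite the unequal sizes.

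**6. Is the sample size touched?** No. It rests on the precision of one proportion. With n = 114 and x = 0.78 × 114 = 88.92, the exact (Clopper-Pearson) limits are the 0.025 quantile of Beta(x, n − x + 1) and the 0.975 quantile of Beta(x + 1, n − x). Their width is 0.159, within the stated 0.16, and 114 is the smallest n that achieves this. For withdrawal, 114 / 0.8 = 142.5, against the stated minimum of 142. No between-group test enters either figure.

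**The case against.** The strongest reply is that the item's declared endpoint is the remission rate, which is binary, and that the sentence goes on to name chi-square or Fisher's exact. Those tests suit independent groups of any size and more than two groups. This stands. A reader who stops at the first half of the sentence might infer that paired tests are used to compare remission between procedures, so that the analysis cannot answer its own question. The document does not support that: remission is not a continuous variable, and the second half supplies a valid test.

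Two other strong readings also fail.

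- A reader might take the unequal group sizes as a fault. They are not. The lack of pairing is what matters, and equal groups would not cure it.
- A reader might infer that procedures will be ranked by their within-group p-values, which would favour the largest group. For the same mean change and standard deviation, the paired t statistic would be √(66/24) = 1.66 times as large in the sleeve group as in either bypass group. The arithmetic is right, but the article nowhere proposes that inference, so it is not counted here.

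It can also be said that a condensed article may leave tests for secondary outcomes to the full protocol or analysis plan. That would excuse silence. The article is not silent: it names specific tests for continuous variables inside a between-group item, and they are the wrong kind. Because before/after change is handled in its own item, the repeated mention has no evident role there other than the group comparison.

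**Conclusion.** Wrong as written, moderate severity. For continuous variables, the item on surgery types and BMI subgroups names only tests that cannot compare those groups, and the article offers no alternative.

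The effect is confined to exploratory aim (ii) and to continuous variables. The primary estimate (one proportion with its 95% confidence interval), the sample size and the comparison of remission rates all stand. No numerical bias can be attached to the defect, because the article does not say how the paired results would be used to compare groups.

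The conclusion rests on two readings: that the continuous-variable clause belongs to the between-group item in which it sits, and that surgery type and BMI group are among the covariates to which chi-square or Fisher's exact applies. If the clause was meant only for before/after change within subgroups, the tests are valid, but the item still gives no between-group comparison of continuous variables and the wording still needs correcting.

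**What to change.** Reword the sensitivity-analysis item as follows.

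1. Keep the paired t-test and signed-rank test for before/after change only.
2. For continuous variables compared between procedures or BMI subgroups (for example %TWL, %EWL, liver fat fraction and liver enzymes), name an independent-samples method: ANOVA or Kruskal-Wallis, or ANCOVA adjusting for the baseline value where one is collected. Table 1 already makes body weight (under demographic data), abdominal MRI and biochemistry mandatory at baseline.
3. Report between-group differences with 95% confidence intervals, not only p-values.
4. State that chi-square or Fisher's exact test compares remission rates across the surgery and BMI groups, so that the reader need not infer it from the word for covariates.

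The choice between ANOVA, Kruskal-Wallis and ANCOVA is for the study team. The necessary change is from paired to independent-samples methods. The cost is a wording amendment: no new data, no added visits and no change to the sample size.
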